## Introduction

 Vaccines are powerful public health tools, significantly reducing illnesses and mortality associated with vaccine-preventable diseases.^1 2^ Childhood vaccinations are especially valuable, as timely immunisation contributes to herd immunity,^3^ limiting the spread of infectious diseases within communities.

Despite their known effectiveness,^4^ coverage of several childhood vaccines has declined worldwide,^5^ falling below the WHO’s 95% recommended threshold.^6^ The UK in particular has experienced a steady decline in the uptake of all childhood vaccines since 2013.^7^ In 2023/2024, coverage in England for the first and second doses of the measles, mumps and rubella vaccine (MMR1 at age 2 years and MMR2 at age 5 years) was 88.9% and 83.9%, respectively.^8^ Liverpool figures were even lower during the same period, with just 81% for MMR1 at age 2 and 73.4% for MMR2 at age 5,^9^ placing the city among the worst performing areas nationally. This has resulted in several outbreaks across England,^10 11^ including a recent cluster of measles cases in Liverpool.^12^

Further compounding this issue are the persistent demographic and socioeconomic inequalities in childhood vaccines uptake.^13^,^16^ Children from deprived communities have notably lower vaccination rates than their peers in more affluent areas, with gaps widening over time.^14^ For instance, the absolute inequality in the uptake of MMR2 between the most and least deprived areas in England widened from 5.3% in 2019 to 11.5% in 2023.^14^

Several factors have contributed to these low and unequal uptake rates, with vaccine hesitancy being among the primary drivers (a delay or refusal to vaccinate despite the availability of vaccines^17^). Hesitancy is often associated with mistrust in healthcare systems, limited engagement with trusted local actors, inadequate communication from healthcare professionals, misinformation and disinformation (deliberate and targeted spreading of misinformation).^18 19^ These factors may intersect with structural barriers, such as inflexible appointment systems, further discouraging the uptake.^19^

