### Intervention details

The intervention targeted parents and carers of children aged 13 months to 5 years and 11 months who were registered with practices in the central and north Liverpool primary care networks (PCNs), areas known for lower childhood vaccination rates and higher levels of deprivation.

Activities were designed and delivered as part of a community-led, creative health approach. The model adapted standard quality improvement (QI) tools for use in community settings and was implemented through establishing a multidisciplinary Community Innovation Team (CIT) comprising community organisations, volunteers, community champions, creatives, primary care and public health professionals. The team received phased training in QI methodology, beginning with the use of local GP data to identify and target populations with low uptake.

To inform intervention design, the CIT conducted a behavioural insight survey with 116 parents and carers of partially or unvaccinated children aged 1–5 years and consulted local health providers involved in childhood vaccination. This was followed by a structured root cause analysis to identify feasible priority actions that tackle root causes locally. Findings revealed widespread concerns about vaccine safety and efficacy, difficulty in identifying misinformation and reduced trust in health authorities and National Health Service (NHS) information. In response, the CIT co-developed a multicomponent intervention to deliver locally relevant health messaging.

The intervention was implemented between 1 September 2023 and 1 June 2024 across central and northern Liverpool. Activities included community outreach events, school-based coffee mornings and a series of reflective discussions, all of which were designed to increase awareness of the MMR vaccine, build trust and support parents and carers in accessing vaccination services. In total, 22 events were held across nine sites. These were supplemented by digital and printed education material, including targeted MMR-related YouTube video links, ‘Measles Machine’ flyers and reminder text messages sent to nearly 2000 parents of partially or unvaccinated children.

Informed by the behavioural insights survey findings, we developed a conceptual diagram representing an a priori hypothesis of how the HELP intervention is expected to influence childhood vaccine uptake (figure 1).

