### Analysis

We will use the SCM, an observational quasi-experimental approach that extends the traditional difference-in-differences (DiD) framework,^27^ to estimate the impact of the intervention on childhood vaccine uptake. While DiD assumes that the intervention and comparison groups would have followed parallel trends in the absence of the intervention, SCM constructs a weighted combination of untreated units, called a ‘synthetic control’, that mirrors the pre-intervention characteristics and outcome trends (ie, vaccine uptake) of the intervention units.^28^ This allows for a more robust estimation of the counterfactual, particularly when the parallel trends assumption is unlikely to hold. This method has been previously used to evaluate the population-level impact of various public health interventions,^34 35^ including those targeting vaccine uptake,^36 37^ demonstrating its suitability for the current study.

GPs will serve as our unit of analysis, with the target population being registered children aged under 5 years who were eligible for routine childhood vaccinations between April 2019 and March 2025, as reported in the COVER dataset. The intervention group is defined as practices whose population-weighted centroids fell within a 1 km radius of any of the nine intervention sites. As such, 19 practices will be included in the intervention group (see figure 2), with all remaining practices in England forming the donor pool for constructing the synthetic control group. We will apply SCM for microdata,^38^ which is specifically suited to settings involving numerous small scale units, such as GPs. Matching will be performed using calibration weights for the pre-intervention uptake of included vaccines and the previously mentioned covariates. The final inclusion of covariates in the SCM will also be guided by their practical contribution to achieving balance between intervention and control units.

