**Figure 2 F2:**
[figure not shown]
Coverage of MMR1 at 2 years and MMR2 at 5 years across Liverpool by MSOA in the year preceding the intervention (April 2022 to March 2023). Red dots with green circles represent the locations of intervention events with a 1 km surrounding buffer, and cyan dots represent the population-weighted centroid of intervention GPs. Coverage data are based on GP-level uptake reported through the COVER programme. COVER, Cover of Vaccination Evaluated Rapidly; GP, general practice; MMR, measles, mumps and rubella; MSOA, Middle Layer Super Output Area.

The pre-intervention period spans Q1 to Q18 (April 2019 to September 2023), with Q19 to Q24 (October 2023 to March 2025) defining the post-intervention period. The average treatment effect will be estimated as the average difference in vaccine uptake between the intervention and synthetic control groups in the post-intervention period.

The statistical significance of estimated effects will be assessed using the permutation inference, following the method described by Robbins and Davenport.^39^ We will perform 250 permutations, reassigning treatment status to control units to generate a distribution of treatment effects under the null hypothesis (ie, no difference in vaccine uptake between the intervention and control groups). All analyses will be conducted using R V.4.4.2 and the microsynth package.^39^

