### Sensitivity analysis

Given the community-based nature of the intervention, there is potential for spillover effects beyond the identified intervention practices. To mitigate this effect, we will conduct a sensitivity analysis excluding other non-intervention GPs located within the central and north Liverpool PCNs from the donor pool practices used to construct the synthetic control group. We will also incorporate a one-quarter lag at the start of the post-intervention period (ie, starts at Q20 instead of Q19) to allow sufficient time for any changes in vaccine uptake to become observable.

To assess the sensitivity of the estimated effect to the exposure’s spatial definition, we will test alternative buffer distances (0.5 km, 1.5 km and 2 km) from intervention event sites. We will further attempt to exclude practices that may have been affected by other concurrent vaccine-related initiatives implemented elsewhere in England. To identify such initiatives, an audit of interventions form will be distributed to immunisation leads at the UK Health Security Agency and to public health leads across the nine local authorities in Cheshire and Merseyside via the Champs Public Health Collaborative. A copy of the form is provided in online supplemental material 1.

Further sensitivity analyses will involve adjusting the pre-intervention period to begin after the final phase of national COVID-19 restrictions in England (February 2022 to Q12 in our dataset), as it could bias the counterfactual estimation. For example, tiered restrictions during the pandemic varied in stringency across England. This has led to regional variation in childhood vaccine uptake^40^ and will consequently affect the SCM matching.

In addition, we will rerun the evaluation using vaccine uptake aggregated to a small area neighbourhood level (LSOA), which may better reflect the community-based nature of the intervention. Finally, to test the robustness of our findings, we will explore alternative approaches to constructing synthetic controls. These may include methods that incorporate negative control series or rely on different assumptions about the counterfactual.

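### The permutation test ignores that the 19 treated practices lie close together in one part of one city; if practices in an area share post-intervention shocks, the p-values for MMR1 and MMR2 are too small

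*Protocol article*

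**What the plan says.** All of this is in the protocol article, Methods and analysis.

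- **Unit** (Analysis): "GPs will serve as our unit of analysis".
- **Treated group** (Analysis): "19 practices will be included in the intervention group", defined as "practices whose population-weighted centroids fell within a 1 km radius of any of the nine intervention sites".
- **Place and time** (Intervention details): "The intervention was implemented between 1 September 2023 and 1 June 2024 across central and northern Liverpool".
- **Donor pool** (Analysis): "all remaining practices in England forming the donor pool for constructing the synthetic control group".
- **Inference** (Analysis, after Figure 2): "We will perform 250 permutations, reassigning treatment status to control units to generate a distribution of treatment effects under the null hypothesis". It follows a cited method and uses the microsynth package. No significance level is stated.
- **Matching** (Analysis): calibration weights on pre-intervention uptake and covariates. The pre-period is Q1 to Q18, ending September 2023, and the effect is averaged over Q19 to Q24.
- **Sensitivity analysis**: changes the donor pool, start lag, buffer radius, pre-period, unit (LSOA) and method of building the synthetic control. None changes how placebo groups are drawn.

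**The concern.** A permutation p-value is valid when the placebo groups are exchangeable with the real one. Here the intervention went to a place, and the treated practices are those near its sites. The natural reading of the inference paragraph is that single practices from a national pool are relabelled as treated. A placebo group formed in that way is scattered, so local influences on uptake largely cancel within it. In 19 practices in one part of one city they need not cancel.

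The protocol gives reasons to expect dependence between neighbouring practices. It anticipates spillover to nearby practices, and its funding and workforce covariates are PCN averages applied to every member practice. It also says of pandemic restrictions that "This has led to regional variation in childhood vaccine uptake". Weights fitted on Q1 to Q18 can absorb persistent area differences, but not new local shocks in the quarters where the effect is measured.

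This permutation is the only inference stated for the two primary outcomes. The protocol also presents the study as a methodological pilot with reusable code, so the same scheme could pass into later evaluations.

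**Working it through.** The protocol states no power, significance level or correlation, so there is no figure of its own to reproduce.

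**Inputs.** From the protocol: m = 19 treated practices and B = 250 permutations. Assumed: a two-sided 5% level, and rho, the residual post-period correlation between practices in the same area after matching, varied from 0 to 0.10.

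**Step 1: one shock shared by all 19 practices.** Relative to a scattered placebo group, the variance of the treated-group mean is inflated by

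DE = 1 + (19 - 1) × rho = 1 + 18 × rho.

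If the critical value comes from the scattered distribution, the actual type I error is

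alpha = 2 × [1 - Phi(1.96 / √DE)].

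**Step 2: shocks acting separately in two sub-areas** of 10 and 9 practices (an assumed split). Then

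DE = 1 + [(10² + 9²)/19 - 1] × rho = 1 + (181/19 - 1) × rho = 1 + 8.53 × rho.

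| rho | DE, one shock | alpha | DE, two sub-areas | alpha |
|---|---|---|---|---|
| 0 | 1.00 | 0.050 | 1.00 | 0.050 |
| 0.02 | 1.36 | 0.093 | 1.17 | about 0.07 |
| 0.05 | 1.90 | 0.155 | 1.43 | about 0.10 |
| 0.10 | 2.80 | 0.241 | 1.85 | about 0.15 |

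**Step 3: simulation check** (4,000 replicates, 300 control areas of 19 practices, 250 permutations, one shock per area).

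| rho | Practices reassigned individually | Whole areas reassigned |
|---|---|---|
| 0 | 0.049 | 0.051 |
| 0.02 | 0.091 | 0.047 |
| 0.05 | 0.142 | 0.044 |
| 0.10 | 0.237 | 0.048 |

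The simulation agrees with Step 1 and shows that reassigning whole areas holds the level near 5%. It does not model the synthetic-control weighting.

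**Step 4: number of draws.** The Monte Carlo standard error at p = 0.05 is √(0.05 × 0.95 / 250) = 0.0138, a 95% range of 0.023 to 0.077. With 5,000 draws the range is 0.044 to 0.056. With p = (b + 1)/251, where b counts the placebo effects at least as extreme as the observed one, the test rejects at 5% when b ≤ 11. Its level under exchangeability is therefore 12/251 = 0.048.

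**The case against.** Several counter-arguments carry weight.

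- **How placebo groups are drawn is not spelled out.** The text says only that status is reassigned to control units, following a cited method. Unrestricted draws of single practices are the natural reading, but a fuller plan could restrict them. This stands as a caveat. The article itself describes no restriction.
- **Rho is unknown.** A reader might infer that the p-values are certainly too small and that the 5% level fails for both primary outcomes. The documents do not show that. Matching on up to 18 quarters may leave little residual correlation, and at rho = 0 there is no inflation. The regional variation the protocol mentions arose in the pandemic, before the intervention, so it enters the matching and does not establish correlation after September 2023.
- **One shock shared by all 19 practices is the least favourable structure.** With two sub-areas the excess is roughly halved. The main donor pool also keeps other Liverpool practices, so a city-wide shock could partly enter the synthetic control, depending on their weights. The formulas ignore this.
- **Confounding is a different problem.** A reader might infer that the Introduction's mention of outbreaks, "including a recent cluster of measles cases in Liverpool", describes a post-intervention shock that would appear as a HELP effect. The cluster is undated, so the documents do not place it after September 2023. A Liverpool-only change coinciding with HELP would in any case bias the estimate, and placebo groups cannot separate the two. The protocol already acknowledges residual confounding, and plans an audit and possibly negative control series.
- **The 250 draws do not make the test invalid.** They limit its precision, and more draws would not cure the clustering.

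None of this makes nationally drawn placebo practices comparable with a geographically selected group.

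**Conclusion.** The concern holds conditionally. As described, the permutation scheme does not reflect the geographic selection of the treated practices, and no planned sensitivity analysis changes it. The LSOA rerun would add more correlated units in the same area. Under any positive residual area correlation after September 2023, the null distribution is too narrow and the p-values for MMR1 and MMR2 are too small.

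The size depends on assumed values: a two-sided 5% level, rho between 0.02 and 0.10, and either one shared shock or two sub-areas. On those assumptions the true error rate lies between about 7% and 24%. These figures are illustrative and do not estimate the error in this study. The number of draws is a separate, minor matter of Monte Carlo precision.

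**What to change.** - **Change the placebo groups.** Form each one to mimic the real selection: for example, take several placebo sites within another urban area or PCN group and select about 19 neighbouring practices close to them. The real group is a union of nine 1 km buffers, so a single contiguous block need not be imposed. Re-estimate the weights and the effect for each group, and rank the HELP effect in that distribution.
- **Keep the unrestricted practice-level permutation** as a comparison, labelled as such.
- **State how placebo groups are drawn and which significance level applies** before analysis begins. The Timeline puts that after the January to April 2026 audit.
- **Raise the number of draws where feasible.** This is the minor part.

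**Cost.** Extra code and computing time, using the planned data sources. Intervals will be wider and p-values less favourable if area correlation is present. The number of independent placebo areas is limited, so overlapping groups add draws but little independent information. It should also be checked that calibration weights can be found for each placebo group. The change does not remove bias from a Liverpool-only event coinciding with HELP, and the report should say so.

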### Sensitivity analysis

Given the community-based nature of the intervention, there is potential for spillover effects beyond the identified intervention practices. To mitigate this effect, we will conduct a sensitivity analysis excluding other non-intervention GPs located within the central and north Liverpool PCNs from the donor pool practices used to construct the synthetic control group. We will also incorporate a one-quarter lag at the start of the post-intervention period (ie, starts at Q20 instead of Q19) to allow sufficient time for any changes in vaccine uptake to become observable.

To assess the sensitivity of the estimated effect to the exposure’s spatial definition, we will test alternative buffer distances (0.5 km, 1.5 km and 2 km) from intervention event sites. We will further attempt to exclude practices that may have been affected by other concurrent vaccine-related initiatives implemented elsewhere in England. To identify such initiatives, an audit of interventions form will be distributed to immunisation leads at the UK Health Security Agency and to public health leads across the nine local authorities in Cheshire and Merseyside via the Champs Public Health Collaborative. A copy of the form is provided in online supplemental material 1.

Further sensitivity analyses will involve adjusting the pre-intervention period to begin after the final phase of national COVID-19 restrictions in England (February 2022 to Q12 in our dataset), as it could bias the counterfactual estimation. For example, tiered restrictions during the pandemic varied in stringency across England. This has led to regional variation in childhood vaccine uptake^40^ and will consequently affect the SCM matching.

In addition, we will rerun the evaluation using vaccine uptake aggregated to a small area neighbourhood level (LSOA), which may better reflect the community-based nature of the intervention. Finally, to test the robustness of our findings, we will explore alternative approaches to constructing synthetic controls. These may include methods that incorporate negative control series or rely on different assumptions about the counterfactual.

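### The 0.5 km buffer run, read with the only donor rule given, lets practices treated in the primary analysis serve as controls; one fixed donor pool should be used in all buffer runs

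*Protocol article*

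**What the plan says.** The Analysis section sets the primary exposure rule: "The intervention group is defined as practices whose population-weighted centroids fell within a 1 km radius of any of the nine intervention sites". The donor rule follows directly: "19 practices will be included in the intervention group (see figure 2), with all remaining practices in England forming the donor pool".

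The Sensitivity analysis section then varies the radius. The aim is "To assess the sensitivity of the estimated effect to the exposure’s spatial definition", and for this "we will test alternative buffer distances (0.5 km, 1.5 km and 2 km) from intervention event sites". Nothing is said about which practices form the donor pool at each of these radii.

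The same section has a separate spillover analysis, which works by "excluding other non-intervention GPs located within the central and north Liverpool PCNs from the donor pool practices". That exclusion is defined by primary care network (PCN), not by distance, and is not said to carry over to the buffer runs.

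**The concern.** The only donor rule in the article makes a control of every practice that is not treated. When the radius shrinks to 0.5 km, some practices that the primary analysis regards as exposed may leave the treated group, and under that rule they enter the donor pool. If the intervention helped them, part of its effect is then subtracted from the effect being estimated.

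These practices could attract real weight. Matching is on earlier uptake and on covariates that include deprivation and ethnicity, and Liverpool is not typical of England. The Introduction gives 81% against 88.9% for MMR1 at age 2 and 73.4% against 83.9% for MMR2 at age 5, gaps of 7.9 and 10.5 points. Neighbouring practices are therefore plausible close matches.

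What is at stake is how the buffer runs are read. A smaller 0.5 km estimate might mean that the result depends on the exposure definition, or only that the controls were partly treated. The two could not be told apart.

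**Working it through.** The protocol gives no figure for the buffer runs, so there is none to reproduce. It does not state how many practices fall within 0.5, 1.5 or 2 km, how many practices England has, or what weights the matching will give. Values used for these below are assumptions.

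**Inputs from the protocol.** 19 treated practices at 1 km (Analysis); estimand is the average post-period difference between the intervention group and the synthetic control (Analysis); anticipated effect 5 to 15 percentage points (Expected results).

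**1. Contamination at 0.5 km.** Let w be the share of synthetic-control weight on practices at 0.5–1 km. Then

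estimate at 0.5 km = effect inside 0.5 km − w × effect at 0.5–1 km.

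With equal effects this is (1 − w) × effect:

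| w | true effect 5 | true effect 15 |
|---|---|---|
| 0.2% | 4.99 | 14.97 |
| 10% | 4.5 | 13.5 |
| 25% | 3.75 | 11.25 |

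If the practices at 0.5–1 km did not benefit, the second term is zero and there is no bias.

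**2. Plausible size of w.** A toy simulation of entropy-balancing weights (assumed 6,000 donors and 12 covariates) gives only a rough guide. When treated practices differed from donors by 0.5 SD on six covariates, mean w was 0.3–0.6% (maximum 1.9%). At 1 SD, with 8 or 12 practices assumed inside 0.5 km, mean w was 6–10% (maximum 25%). The 1 SD case with 4 practices inside 0.5 km, and every case at 1.5–2 SD, failed numerically and are not used. So w may be negligible or material, and the document cannot settle which.

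**3. Do nested circles lose the distance information?** Not if donors are clean. With n practices inside 0.5 km,

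effect at 0.5–1 km = (19 × estimate at 1 km − n × estimate at 0.5 km) / (19 − n).

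Take n = 8 (assumed), with true effects of 10 inside and 2 outside. The 1 km estimate is (8 × 10 + 11 × 2)/19 = 5.37, and differencing returns (102 − 80)/11 = 2.0, which is correct.

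Now let the true effect be 5 in both zones, with w = 25% in the 0.5 km run and clean donors in the 1 km run. The 0.5 km estimate is 3.75, and differencing gives (19 × 5 − 8 × 3.75)/11 = 65/11 = 5.9. A flat effect would appear as 3.75 inside and 5.9 outside. The shifting donor pool causes this; the nesting does not.

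**4. Wider buffers.** If the effect were confined to the 19 practices and a wider buffer held N practices, the estimate would be effect × 19/N. For 5 points and assumed N of 25 or 40 this gives 5 × 19/25 = 3.80 or 5 × 19/40 = 2.4. The confinement is itself an assumption. If practices at 1–2 km were also exposed, widening the buffer would bring exposed practices into the treated group and take them out of the controls, which could raise the estimate.

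**The case against.** The strongest reply is that the donor rule is stated for the 1 km analysis only, so applying it to the other radii is an inference, and that an article may leave such detail to a fuller plan. It is an inference, but it rests on the only rule given, and that rule behaves badly when the radius shrinks. The PCN exclusion shows that the authors recognise the risk of exposed donors. Practices that lose treated status at 0.5 km might even fall under its wording, but the text does not join the two analyses.

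Several objections stand and limit the point. The stated aim is sensitivity to the spatial definition, and no distance-response curve is promised. If the effect is concentrated very close to the sites, practices at 0.5–1 km carry little of it and contaminate little. The bias is toward zero, so it would not manufacture an effect. With a national donor pool, w may be trivial.

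A reader might also infer that the wider runs must understate the effect. The documents do not support that. The intervention was aimed at families registered across the central and north Liverpool PCNs and included "reminder text messages sent to nearly 2000 parents of partially or unvaccinated children", so practices beyond 1 km may well have been exposed.

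**Conclusion.** The point holds in a limited form. On the plain reading, the 0.5 km run admits as controls any practices at 0.5–1 km that the primary analysis treats. If those practices benefited, the estimate is pulled toward zero, by the fraction w when effects are equal. At 10% and 25% weight, 5 points becomes 4.5 and 3.75; at 0.2% the loss is invisible. All values of w are assumptions. Since treated group and donor pool move together, a difference between radii has no single interpretation.

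It would go too far to conclude that the buffer runs can say nothing about distance, or that a local effect is bound to look fragile at both ends. Nested estimates can be differenced when donors are clean, and full-size bias at both ends needs an effect that is flat to 1 km and zero beyond, which the document does not claim. The primary estimate is not touched by this point. Severity is minor.

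**What to change.** State in the Sensitivity analysis section that all buffer runs use one fixed donor pool excluding every practice within 2 km of any intervention site. Add a 1 km run against that pool, so that 0.5, 1, 1.5 and 2 km are compared on the same controls. Say also whether the PCN exclusion applies to these runs.

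If a distance gradient is to be interpreted, disjoint rings (0–0.5, 0.5–1, 1–1.5 and 1.5–2 km) against the same donor pool would show it directly. This is optional, and the smaller groups mean wider intervals.

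The cost is a sentence or two of protocol text, a few reruns of existing code, and the loss of a small number of local donors, some of which may be good matches, from a national pool. The Timeline section places the analysis after the January to April 2026 audit, so the rule can be fixed before any results are seen.
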